### Compare pyrosequencing and LAMP for the assessment of SNPs linked to BZ resistance

The sensitivity of the LAMP method to detect mutant SNPs linked to BZ resistance will be evaluated using the pyrosequencing method as the gold standard. The impact of SNP frequency on the sensitivity of LAMP will be explored by a logistic regression model with the LAMP result as outcome (negative/positive) and the frequency of SNPs linked to BZ resistance as covariate. The predictive power of the final models will be evaluated by the proportion of the observed outcome that was correctly predicted by the model. To this end, an individual probability >0.5 will be set as a positive test result, and negative in all other cases. The sensitivity for each of the pre-defined values of FEC will be calculated based on these models.

Finally, the κ-statistic will be determined to assess the agreement in the LAMP test result across the different study sites, Canada (McGill University), Ethiopia (Jimma University) and Tanzania (Public Health Laboratory—Ivo de Carneri)). The value of this statistic indicates a slight (κ <0.2), fair (0.2 ≤ κ <0.4), moderate (0.4 ≤ κ <0.6), substantial (0.6 ≤ κ <0.8) and an almost perfect agreement (κ ≥ 0.8).

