#### LAMP

A previously described LAMP protocol [65] will be applied on a subset of 300 DNA samples that are withheld for pyrosequencing. The selection of these samples will be based on the frequency of SNPs linked to AR. Based on the pyrosequencing results, samples will be classified into four levels of SNP frequency, including absence of SNP linked to BZ resistance, and low, moderate and high frequency of SNPs linked to BZ resistance. The thresholds used to define the last three levels of frequency of SNPs will be based on the 1^st^ and 3^rd^ quartile of the frequency of SNP across all the samples, in which SNP linked to BZ resistance are present. Samples in which the frequency of a SNP for BZ resistance is higher than 0% but lower than the 1^st^ quartile will be classified into the low frequency group, samples in which the frequency of a SNP for BZ resistance is at least equal to the 3^rd^ quartile will be classified into the high frequency group. All other samples, in which SNPs linked to BZ resistance are found, will be classified into the moderate frequency group. For each STH species (*Ascaris*, *Trichuris*, and hookworms), 25 samples in each level of SNP frequency will be randomly selected and processed with the LAMP assay. The LAMP will be performed at McGill University (Canada) and at two study sites (Ethiopia and Tanzania).

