#### Pooling stool samples for DNA-based diagnostic methods

For both qPCR and pyrosequencing/LAMP, pooled samples will be analyzed. For qPCR, aliquots of all stool samples preserved for further molecular analysis will be pooled into pools of 10, 20 and 60 individual samples. The procedure to pool stool was adapted from Mekonnen et al., [66]. A detailed SOP on sample pooling is available in supplementary information (S10 Info). For pyrosequencing and LAMP, only samples that are withheld for pyrosequencing will be pooled into pools of 10 individual samples. All downstream processes (DNA extraction extracted, qPCR and pyrosequencing/LAMP) will be performed as described in aforementioned sections.

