### Assess the diagnostic performance of Kato-Katz thick smear, Mini-FLOTAC, FECPAK^G2^ and qPCR

For each diagnostic method, the sensitivity will be calculated using the combined results of the four methods (duplicate Kato-Katz thick smear, Mini-FLOTAC, FECPAK^G2^ and qPCR) as the diagnostic ‘gold’ standard. This means that a sample is considered positive if it tested positive on at least one of the four methods. The species specificity of all methods will be set at 100%, as indicated by the morphology of the eggs or by the species-specific primer sets used in qPCR. The corresponding 95% CI for sensitivity will be calculated separately for each diagnostic method. Differences in sensitivity between methods will be assessed by a permutation test (10,000 iterations). Tukey’s method will be applied for pair-wise comparisons between the methods. The impact of infection intensity on the sensitivity within each method will be explored by a logistic regression model, which will be fitted for each of the methods with their test result (positive/negative) as the outcome and the natural log transformed mean FEC across the three methods as covariate. The predictive power of the final models will be evaluated by the proportion of the observed outcome that was correctly predicted by the model. To this end, an individual probability >0.5 will be set as a positive test result, and negative if different. Finally, the sensitivity for each of the pre-defined values of FEC will be calculated based on these models.

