### Assess pooling samples as a cost-saving strategy to determine infection intensity (qPCR) and occurrence of SNPs linked to BZ resistance (pyrosequencing and LAMP)

For qPCR, we will apply the Pearson’s correlation coefficient to assess the agreement between the mean frequency of GE number based on the examination of individual samples and the GE based on the examination of pooled samples will be evaluated. In addition, a permutation test (10,000 iterations) will be applied to test for differences in mean GE number between the examination of individual and pooled samples.

For pyrosequencing, the agreement between the mean frequency of SNPs based on the examination of individual samples and the frequency of SNPs based on the examination of pooled samples will be evaluated by the Pearson’s correlation coefficient. In addition, a permutation test will be applied to test for differences in mean frequencies between examination of individual and pooled samples.

For LAMP, the κ-statistic will be determined to assess the agreement in the LAMP test results obtained by an individual and a pooled examination strategy. The impact of SNP frequency on the sensitivity of LAMP will be explored by a logistic regression model with the LAMP result as outcome (negative/positive) and the frequency of SNPs linked to BZ resistance as covariate. The predictive power of the final models will be evaluated by the proportion of the observed outcome that was correctly predicted by the model. To this end, an individual probability >0.5 will be set as a positive test result, and negative in all other cases. The sensitivity for each of the pre-defined values of SNP frequency will be calculated based on these models.

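### The LAMP section asks for sensitivity at egg-count values from a model that contains only SNP frequency, and LAMP specificity, pooling agreement and LAMP pool membership need tighter definition

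*Protocol article*

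**What the plan says.** **LAMP against pyrosequencing.** In the statistical section comparing the two assays, pyrosequencing is the gold standard and sensitivity is the only accuracy measure named. A logistic model has the LAMP result as outcome and "the frequency of SNPs linked to BZ resistance as covariate". The paragraph ends: "The sensitivity for each of the pre-defined values of FEC will be calculated based on these models".

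**The same sentence elsewhere.** The section on diagnostic performance of the egg counts and qPCR ends with "Finally, the sensitivity for each of the pre-defined values of FEC will be calculated based on these models", after a model with "the natural log transformed mean FEC across the three methods as covariate". The pooling section repeats the LAMP model and ends with "The sensitivity for each of the pre-defined values of SNP frequency will be calculated based on these models".

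**Samples.** The LAMP laboratory section takes 300 samples from those kept for pyrosequencing, in four levels of SNP frequency including absence. For each species, "25 samples in each level of SNP frequency will be randomly selected and processed with the LAMP assay".

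**Pools.** For pyrosequencing and LAMP, "only samples that are withheld for pyrosequencing will be pooled into pools of 10 individual samples". For qPCR the pools hold 10, 20 and 60 samples.

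**Pooling statistics.** For qPCR the pooling section plans to use Pearson's "correlation coefficient to assess the agreement between the mean frequency of GE number based on the examination of individual samples" and the pooled result. Pyrosequencing is handled the same way. Each is paired with a permutation test of the mean difference. Pooled LAMP is compared with individual LAMP by kappa.

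**The concern.** Objective 6 (LAMP against pyrosequencing) ends in an output that its model cannot produce.

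The introduction wants resistance found early, when mutant frequency is low and false positives matter most. Yet no error rate is named for the SNP-free samples that are tested.

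Objective 7 (pooling) asks whether a pooled result can stand in for individual results. That is a question of agreement, and Pearson's r measures linear association. A pooled assay that reads half the true value everywhere would still give r = 1.

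For pooled LAMP, the article does not say which samples fill the pools or how ten individual results become the comparator for one pooled result. Depending on the choice, kappa either lacks individual results for most pool members or has almost no negative pools.

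**Working it through.** **1. Model and prediction side by side.**

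| Section | Covariate | Sensitivity reported at |
|---|---|---|
| Egg counts and qPCR | ln mean FEC | FEC |
| LAMP against pyrosequencing | SNP frequency | FEC |
| Pooled LAMP | SNP frequency | SNP frequency |

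Only the middle row does not match. It looks like a carry-over from the first.

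**2. LAMP sample count and specificity.** The plan's total reproduces: 3 species × 4 levels × 25 = 300, or 100 per species. SNP-free samples: 3 × 25 = 75. If all n are LAMP-negative, the exact two-sided 95% lower bound is 0.025^(1/n):
- n = 75: 0.952
- n = 25: 0.863

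**3. Size of the pyrosequenced set.** Inputs are the minima in the pyrosequencing section, per species over four sites:
- First subset: 60 × 4 = 240.
- Second subset: (30 cured + 2 × 30 not cured) × 4 = 360.
- No overlap: 240 + 360 = 600.
- All second-subset baseline samples already in the first: 240 + 30 × 4 = 360.

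**4. LAMP pools filled at random from that set** (an assumption; the article gives no allocation rule). Expected members with an individual LAMP result: 10 × 100/600 = 1.7 to 10 × 100/360 = 2.8. The chance that all ten have one is C(100,10)/C(N,10) = 1.9 × 10⁻⁶ at N = 360 and 1.1 × 10⁻⁸ at N = 600.

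**5. LAMP pools filled at random from the 100 tested samples of a species.** By design 75 of 100 carry a SNP. The chance of a pool with no SNP-positive member is C(25,10)/C(100,10) = 1.9 × 10⁻⁷. Kappa compares LAMP with LAMP, so the chance of no LAMP-positive member also matters. With an assumed sensitivity s and no false positives it is about (1 − 0.75s)^10:
- s = 0.3: 0.078
- s = 0.5: 0.009
- s = 0.7: 0.0006

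There are at most 100/10 = 10 non-overlapping pools per species, so negative pools would be rare or absent unless LAMP sensitivity is low.

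**6. Pearson's r and pool size (qPCR only).** Set true between-sample variance to 1, with assay error variance e and random pools of size k. The document gives no value for e.

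If pooled-assay error stays at e, r = (1/k) / √[(1/k + e/k)(1/k + e)]. If it shrinks to e/k, r = 1/(1 + e).

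| Assumption | k = 10 | k = 20 | k = 60 |
|---|---|---|---|
| No error | 1.00 | 1.00 | 1.00 |
| Fixed pooled error, e = 0.05 | 0.80 | 0.69 | 0.49 |
| Fixed pooled error, e = 0.25 | 0.48 | 0.37 | 0.22 |
| Shrinking pooled error, e = 0.25 | 0.80 | 0.80 | 0.80 |
| Pools grouped by intensity, fixed e = 0.25 (simulated) | 0.89 | 0.90 | 0.90 |
| Lognormal, log-SD 1.5, proportional error log-SD 0.5 (simulated, 1,200 samples) | 0.69 | 0.62 | 0.47 |
| Same, error log-SD 0.1 | 0.98 | 0.98 | 0.95 |

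So r can differ between pool sizes with the same assay, but it need not.

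**The case against.** The strongest reply is that the FEC sentence is a slip. The parallel sentence in the pooling section shows what was meant, one word corrects it, and no sample or number changes. That stands: it is a wording error, not a design fault.

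Three stronger readings are tempting, and the documents do not support them.

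- *A reader might infer that the LAMP and pooling analyses cannot be run.* Most can: LAMP sensitivity, the logistic model, between-laboratory kappa and the mean-difference tests. Pooled kappa can also be computed if pools are confined to the 300 tested samples, which the article neither requires nor excludes. The pooling procedure is in a supplement that is not shown.
- *A reader might infer that r must fall as pools grow, so that pool sizes will be ranked by an artefact.* The table above shows that the fall depends on assay error and on how pools are formed. The article nowhere says that it will rank pool sizes by r.
- *A reader might infer that LAMP false positives go unexamined.* If the SNP-free samples enter the logistic model, its fitted probability at frequency zero is the false-positive rate. But the section labels its output sensitivity, and a directly reported proportion is clearer.

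The mean-difference test does address average bias. A non-significant result still does not show agreement, and the test says nothing about scatter of individual pools.

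**Conclusion.** The point holds in a limited form. The prediction at FEC values contradicts the model in the same paragraph, whatever an analysis plan or supplement may add. Pearson's r is the wrong statistic for the agreement claimed for qPCR and pyrosequencing pools; this rests on no assumption. Any difference in r between pool sizes does rest on assumptions about assay error and allocation that the document does not give.

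LAMP specificity can be had from samples already in the design, with a lower bound of about 95% at best for the three species together and about 86% for one.

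For pooled LAMP, what stands is that the text does not link the pools to the individually tested samples. Under random filling, neither source of pools gives a useful kappa: on average 1.7 to 2.8 tested members of 10 in one case, almost no SNP-free pools in the other. These figures use the stated minimum sample numbers. The consequences are confined to objectives 6 and 7; the egg reduction rate comparison is untouched.

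**What to change.** 1. In the section comparing LAMP with pyrosequencing, replace FEC by SNP frequency in the last sentence on the logistic model.
2. Add LAMP specificity in the SNP-free samples, by species and overall, with exact 95% intervals.
3. For qPCR and pyrosequencing pools, replace Pearson's r as the measure of agreement by the pooled result set against the mean of its individual results: log-ratio for GE, difference for SNP frequency. Give the mean and limits of agreement for each pool size.
4. Form LAMP pools only from individually LAMP-tested samples of one species, fix the number of SNP-positive members in advance, and report pool detection by expected SNP frequency instead of relying on kappa.

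The composition in step 4 must fit 25 SNP-free samples per species. One pool each with 0, 1, 2 and 5 positive members would need 10 + 9 + 8 + 5 = 32, which is too many. Pools with 0, 1 and 5 positives need 10 + 9 + 5 = 24, which fits. The alternative is to reuse negatives, declare it, and allow for the dependence between pools.

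Cost: steps 1 to 3 are wording and slightly more analysis. Step 4 needs a stated pool plan but no new participants; its downside is a small number of low-frequency pools, so detection there will be imprecise.

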### Assess pooling samples as a cost-saving strategy to determine infection intensity (qPCR) and occurrence of SNPs linked to BZ resistance (pyrosequencing and LAMP)

For qPCR, we will apply the Pearson’s correlation coefficient to assess the agreement between the mean frequency of GE number based on the examination of individual samples and the GE based on the examination of pooled samples will be evaluated. In addition, a permutation test (10,000 iterations) will be applied to test for differences in mean GE number between the examination of individual and pooled samples.

For pyrosequencing, the agreement between the mean frequency of SNPs based on the examination of individual samples and the frequency of SNPs based on the examination of pooled samples will be evaluated by the Pearson’s correlation coefficient. In addition, a permutation test will be applied to test for differences in mean frequencies between examination of individual and pooled samples.

For LAMP, the κ-statistic will be determined to assess the agreement in the LAMP test results obtained by an individual and a pooled examination strategy. The impact of SNP frequency on the sensitivity of LAMP will be explored by a logistic regression model with the LAMP result as outcome (negative/positive) and the frequency of SNPs linked to BZ resistance as covariate. The predictive power of the final models will be evaluated by the proportion of the observed outcome that was correctly predicted by the model. To this end, an individual probability >0.5 will be set as a positive test result, and negative in all other cases. The sensitivity for each of the pre-defined values of SNP frequency will be calculated based on these models.

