### Sample size calculation

A sample size was calculated to test the alternative hypothesis that FECPAK^G2^, Mini-FLOTAC and single Kato-Katz thick smear provide equivalent drug efficacy results measured by ERRs compared to a duplicate Kato-Katz thick smear. Given the differences in drug efficacy of ALB across the STH species [15, 21] (*Ascaris*: ~99%, hookworms: ~96%, *Trichuris*: ~65%), a level of equivalence that is acceptable for *Trichuris* may not be acceptable for *Ascaris*. Therefore, a species-specific level of equivalence was used. For *Ascaris* the level of equivalence was set at 2.5-point percentage, for hookworms and *Trichuris* the level of equivalence was set at 5.0 and 10 point percentage, respectively. Both type I and II errors were set at 0.05.

To calculate the corresponding sample size for each of the STH species, we performed a simulation study. This simulation study considered (i) variation in ERR and baseline FECs across and within STH species, (ii) variation in FECs introduced by the egg counting process, (iii) the paired ERR results across egg count methods, and (iv) a post-hoc correction for a pair-wise comparison. Based on the simulation, at least 110, 100 and 12 complete cases are required for *Trichuris*, hookworm and *Ascaris*, respectively. A detailed description of the sample size calculation is available in the supplementary information (S1 Info).

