#### Pyrosequencing

In two subsets of the DNA samples, we will apply a previously described pyrosequencing protocol [30, 52] to determine frequency of mutant SNPs in the three codons of the ß-tubulin associated with BZ resistance. The first subset will consist only of baseline DNA samples, and will be used to assess the association between drug pressure history and the corresponding frequency of mutant SNPs linked to BZ resistance. Per study site, 60 baseline DNA samples positive for each STH species (*Ascaris*, *Trichuris* and hookworm) will be randomly selected from the available baseline DNA samples. To avoid these samples representing one school or one level of individual response to ALB, selection of the samples will be proportionately to the total number of cases per school and individual drug response (Table 3).

**Table 3 pntd.0006912.t003:** Classification of the individual response to a single oral dose 400 mg ALB against STH based on the individual egg reduction rate (iERR).

STH	Cured	Responder	Poor responder	Non-responder
***Ascaris***	iERR = 100%	iERR ≥ 95%	85% ≤ iERR < 95%	iERR < 85%
***Trichuris***	iERR = 100%	iERR ≥ 50%	40% ≤ iERR < 50%	iERR < 40%
**Hookworms**	iERR = 100%	iERR ≥ 90%	80% ≤ iERR < 90%	iERR < 80%

We will use a second set of DNA samples to assess the association between individual responses to ALB by pyrosequencing the ß-tubulin gene. At each site, samples from at least 30 participants who were cured (baseline samples only) and from at least 30 participants who were still excreting eggs at follow-up (both baseline and follow-up samples) will be selected for each STH species separately. Participants which still excreted eggs will be stratified, into ‘responders’, ‘poor responders’ and ‘non-responders’. This stratification will be based on WHO thresholds used for classifying the efficacy into ‘satisfactory’ (‘responders’), ‘doubtful’ (‘poor responders’) and ‘reduced’ (‘non-responders’) [27] (Table 3). A total of 10 participants will be randomly selected for each stratum. Total DNA will be extracted from these stool samples and sent for pyrosequencing at McGill University (Canada).

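### Pooling for qPCR and pyrosequencing is judged by Pearson's r, which misses a proportional loss, and by a test of difference with no stated pairing; neither estimates pooling bias

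*Protocol article*

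**What the plan says.** The section on pooling stool samples for DNA-based methods says that for qPCR "aliquots of all stool samples preserved for further molecular analysis will be pooled into pools of 10, 20 and 60 individual samples". For pyrosequencing and LAMP, "only samples that are withheld for pyrosequencing will be pooled into pools of 10 individual samples". Pool and individual results therefore come from the same stools.

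The analysis section on pooling plans two things for qPCR. The first is a Pearson coefficient for "the agreement between the mean frequency of GE number based on the examination of individual samples and the GE" of the pooled samples. The second is a test: "a permutation test (10,000 iterations) will be applied to test for differences in mean GE number between the examination of individual and pooled samples". The pyrosequencing paragraph again plans a Pearson coefficient, and "a permutation test will be applied to test for differences in mean frequencies between examination of individual and pooled samples". LAMP is assessed by kappa.

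The section does not say what is permuted, and it neither states nor excludes pairing of a pool with its members. It gives no margin, and no estimate or interval for the difference between pooled and individual results.

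**The concern.** The pooling objective needs to know whether a pool returns the same answer as the average of its members. The likely failure is systematic, for example DNA lost or diluted below what the members show.

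Pearson's r cannot see a constant proportional loss, which leaves the permutation test as the only planned check for it. If that test shuffles labels across all results, spread between children sets the width of the null distribution. The observed difference contains almost none of that spread, because the same children sit on both sides. A moderate loss then looks compatible with chance.

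A non-significant result is what would favour pooling, so a weak test favours the cheaper strategy. The aim of the study is to recommend methods to control programs.

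**Working it through.** **Plan's own figure.** There is none to reproduce. The article gives no sample size, effect size or margin for pooling. "Both type I and II errors were set at 0.05" refers to the ERR equivalence calculation; two-sided 0.05 is assumed here.

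**Pearson's r.** If the pool returns c times the member mean x, with c > 0, then r = c·Var(x) / (SD(x)·c·SD(x)) = 1 for every c. A 50% loss (c = 0.5) leaves r unchanged.

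**Why pairing matters: a hand calculation.** Assume GE log-normal with log SD 1.5, and 120 samples in 12 pools of 10. The coefficient of variation between children is √(e^2.25 − 1) = 2.91. In units of the mean GE:
- Individuals versus pools, labels shuffled: null SE about 2.91 × √(1/120 + 1/12) = 0.88.
- Pool means versus pools, labels shuffled: null SE about (2.91/√10) × √(2/12) = 0.38.
- Within pool: only assay error remains. With 30% assay error the SE, obtained by simulation, is about 0.15.

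A 30% loss is a difference of 0.30. That is about 0.3, 0.8 and 2.0 standard errors. These are rough guides because the data are skewed.

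**Simulation, GE.** Assumptions, none of them in the article: log SD 1.5 or 2.0, assay error 0.3 on the log scale, and a constant proportional loss. A = individuals versus pools; B = pool means versus pools; C = within-pool sign-flip on differences. Power at 0.05:

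| Samples, pools | Log SD | Loss | A | B | C |
|---|---|---|---|---|---|
| 120, 12 of 10 | 1.5 | 25% | 0.00 | 0.05 | 0.72 |
| | 1.5 | 50% | 0.00 | 0.62 | 1.00 |
| | 2.0 | 25% | 0.00 | 0.00 | 0.53 |
| | 2.0 | 50% | 0.00 | 0.25 | 0.98 |
| 120, 6 of 20 | 1.5 | 25% | 0.00 | 0.06 | 0.35 |
| | 2.0 | 50% | 0.00 | 0.23 | 0.88 |
| 480, 48 of 10 | 1.5 | 25% | 0.00 | 0.35 | 0.98 |
| | 1.5 | 50% | 0.03 | 0.98 | 1.00 |
| | 2.0 | 25% | 0.00 | 0.02 | 0.92 |
| | 2.0 | 50% | 0.00 | 0.75 | 1.00 |

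With no loss, A and B reject in 0.00 of trials and C in 0.04 to 0.06.

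At a 30% loss (pools of 10 or 20, 120 to 480 samples), log SD 1.7 gives 0% for A, 4-34% for B and 47-100% for C. The ranges depend on the assumed spread: over log SD 1.5 to 2.0, a rerun gives 0%, 2-61% and 42-100%. At larger losses the unpaired tests recover. At 75%, B reaches 0.80 to 1.00; at 90% with 480 samples in pools of 10, A reaches 0.24 to 0.78.

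**Simulation, SNP frequency.** The first pyrosequencing subset has "60 baseline DNA samples positive for each STH species" per site: 60/10 = 6 pools per site and species, and 4 × 6 = 24 over four sites. Assumed: Beta(0.3, 1.2) or Beta(1, 4) frequencies, measurement SD 0.03.

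| Pools | Loss | A | B | C |
|---|---|---|---|---|
| 6 | 25% | 0.00 | 0.09-0.31 | 0.66-0.69 |
| 6 | 50% | 0.00-0.02 | 0.78-0.99 | 0.94-0.96 |
| 24 | 25% | 0.00-0.01 | 0.88-1.00 | 1.00 |
| 24 | 50% | 0.61-1.00 | 1.00 | 1.00 |

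Under Beta(0.3, 1.2) with no loss, C rejected in 0.09 with 24 pools and 0.19 with 72. Cutting individual frequencies off at zero creates a real small bias in those simulated data.

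**Few pools.** With m pools the smallest two-sided sign-flip p is 2/2^m: 2/2² = 0.50 for 2 pools, 2/2⁵ = 0.0625 for 5, and 2/2⁶ = 0.031 for 6. Six pools of 60 need 6 × 60 = 360 samples. The only size guide is "at least 110, 100 and 12 complete cases are required for" *Trichuris*, hookworm and *Ascaris*, and 110 samples make one full pool of 60.

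**The case against.** The strongest reply is that the article never says the test is unpaired. A reader might infer that it is, but that would be an inference from silence. A within-pool permutation fits the wording, the correlation beside it already needs each pool matched to its members, and the sample-size section shows that the authors recognise paired data elsewhere. A condensed article may leave the permutation scheme to the full plan. This stands: the missing scheme alone would be a request for clarification.

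A reader might also infer that a biased pooling procedure would almost never be detected. The figures do not support that. It holds for individuals versus pools at losses up to about 50% in GE. It fails for pool means versus pools at 50% loss with many pools, for very large losses, and for SNP frequency at 50% loss with 24 pools. In some SNP settings with 6 pools, the unpaired comparison of pool means even does slightly better than the sign-flip.

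The reply is also right that pairing cannot rescue a test on fewer than 6 pools. A log ratio is undefined when GE is zero, and zeros are likely because all follow-up samples are preserved whatever their egg count. Finally, the article sets no rule that non-significance means success.

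One part of the concern survives all of this. Whichever scheme is used, the stated outputs are a correlation that ignores proportional bias and a p-value for a difference. Neither says how large the pooling bias is or could be.

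**Conclusion.** The point holds in a limited form. As described, the analysis for qPCR and pyrosequencing can neither show that pooled and individual results agree nor bound the bias.

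If the test ignores the pools, it has little power for moderate GE losses: at 30% loss, 0% for individuals versus pools and about 4-34% for pool means versus pools, against about 47-100% within pool with 6 or more pools. These sizes rest on an assumed log-normal spread, assay error and constant loss, and the middle range in particular moves with the spread. The invariance of r, the limit of 6 pools, and the fact that non-significance is not agreement need no such assumptions.

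Pools of 60 are the weakest case under any test unless samples are combined over sites or time points. The LAMP comparison is not affected.

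**What to change.** In the analysis section on pooling, replace both tests of means by a within-pool comparison: the pooled result against the arithmetic mean of that pool's own members.

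- Report, separately by pool size, the mean difference or the ratio of means with a 95% CI over pools.
- For GE, use a log ratio only where both values are positive, and state a rule for zeros, such as the ratio of summed GE with pools resampled.
- Judge pooling on the interval and not on a non-significant p-value. It helps to state beforehand what loss would be tolerable.
- If a test is kept, permute within pool, and do not interpret it for pool sizes with fewer than 6 pools.

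The cost is wording only, since the planned correlation already needs the link between pools and members. The downside is a wide interval for pools of 60, and none at all where only one such pool can be formed.

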#### qPCR

All DNA extracts will be analyzed for the presence of *A*. *lumbricoides*, *T*. *trichiura*, *N*. *americanus* and *A*. *duodenale* DNA using qPCR assays previously described [37, 63, 64]. S9 Info provides a detailed SOP on how we will perform the qPCR. The output of the qPCR analysis will be expressed in genome equivalents (GE) per ml DNA extract.

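### Pooled SNP frequency is compared only with the plain mean of individual frequencies, so intensity weighting cannot be told apart from assay or pooling failure

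*Protocol article*

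**What the plan says.** The statistical section on pooling as a cost-saving strategy sets the pyrosequencing comparison: "the agreement between the mean frequency of SNPs based on the examination of individual samples and the frequency of SNPs" measured in the pools. The statistic named for this agreement is Pearson's correlation. The section adds that "a permutation test will be applied to test for differences in mean frequencies between examination of individual and pooled samples". No weighting of the individual frequencies is stated, so the plain reading is a simple average over the samples in the pool.

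The section on pooling stool samples says that for pyrosequencing and LAMP "only samples that are withheld for pyrosequencing will be pooled into pools of 10 individual samples". For qPCR it states that "aliquots of all stool samples preserved for further molecular analysis will be pooled into pools of 10, 20 and 60 individual samples". It then says "All downstream processes (DNA extraction extracted, qPCR and pyrosequencing/LAMP) will be performed as described in aforementioned sections", which places DNA extraction after pooling. The pooling procedure itself is left to S10 Info, which is not shown.

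The qPCR section has all DNA extracts analysed and states: "The output of the qPCR analysis will be expressed in genome equivalents (GE) per ml DNA extract". A measure of worm DNA per individual sample is therefore already planned.

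**The concern.** An allele frequency is a ratio. When stool aliquots are mixed and extracted together, each child contributes template in proportion to the worm DNA in the aliquot, so a heavily infected child counts for more than a lightly infected one. The planned reference gives every child the same weight. The two quantities generally differ when both DNA quantity and SNP frequency vary within a pool.

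The qPCR comparison in the same section does not have this difficulty: for equal aliquots, the arithmetic mean of GE is what a pool should return. The same template does not carry over to a SNP frequency.

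At stake is the reading of one stated objective, whether pooling can save cost in SNP surveillance. If the correlation is modest or single pools disagree, the planned analysis cannot say whether the laboratory procedure failed or whether the pool correctly measured a different average. These call for different responses. If SNP frequency is related to infection intensity, the mean difference is also systematic and again cannot be attributed.

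**Working it through.** The protocol gives no figure for this comparison, so there is none to reproduce.

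**Algebra.** For sample i in a pool of 10, let w_i be its target DNA and p_i its SNP frequency.
- Error-free pooled reading: sum(w_i p_i) / sum(w_i).
- Planned reference: sum(p_i) / 10.
- Gap: cov(w, p) / mean(w), taken within the pool. It is zero only if w or p is constant in the pool, or the two are uncorrelated in it.

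**Illustration from the protocol's own limits.** The baseline preservation threshold is 13 eggs on duplicate Kato-Katz (stool preservation section), and counts are multiplied by 12 (Kato-Katz section): 13 × 12 = 156 eggs per gram (EPG). The intensity section classes *Ascaris* as moderate from 5,000 EPG and heavy above 49,999 EPG. Let egg output stand in for DNA (an assumption). Put one heavier sample among nine at 156 EPG (9 × 156 = 1,404), and let only that sample carry the SNP, at 50%. The plain mean is 50% / 10 = 5%.

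| Heavier sample (EPG) | Its share of the pool | Exact pooled reading |
|---|---|---|
| 1,000 | 1,000 / 2,404 = 41.6% | 20.8% |
| 5,000 | 5,000 / 6,404 = 78.1% | 39.0% |
| 50,000 | 50,000 / 51,404 = 97.3% | 48.6% |

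This is a constructed extreme. It shows the mechanism, not an expected result. The EPG limits are classification cut-offs, not an observed distribution.

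**Simulation with no assay error.** Assumptions not in the protocol: log-normal DNA quantity with log-SD 0.5 to 2, and Beta-distributed individual SNP frequencies. DNA quantity and SNP frequency are independent unless stated. The table gives Pearson's r between the exact pooled reading and the plain mean.

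| Expected SNP frequency | log-SD 0.5 | 1.0 | 1.5 | 2.0 |
|---|---|---|---|---|
| 25% in every pool | 0.90 | 0.72 | 0.58 | 0.50 |
| Sites 10/20/30/40% (Beta precision 3) | 0.97 | 0.90 | 0.82 | 0.76 |
| Sites 5/15/30/50% (Beta precision 3) | 0.99 | 0.95 | 0.90 | 0.86 |

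With 25% in every pool, the mean absolute gap per pool is 1.7–2.9, 3.3–5.8, 4.9–8.4 and 6.0–10.4 percentage points across the four log-SDs. The range covers Beta(2,6) to Beta(0.5,1.5).

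**Mean difference.** The Pyrosequencing section plans "Per study site, 60 baseline DNA samples positive for each STH species", so 60 / 10 = 6 pools per species and site and 24 over four sites, if all are pooled. The simulation used 24 pools, mean SNP frequency 15% (or sites at 3, 5, 15 and 40%), Beta precision 3 and a paired sign-flip permutation test.
- DNA quantity and SNP frequency independent: the mean difference is about 0 and the test rejects in about 4% to 10% of runs.
- Assumed correlation of ±0.3 between SNP frequency and log DNA: the mean difference lies between about −5 and +8 percentage points and the test rejects in about 84% to 99% of runs, with no assay error at all.

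**The weighted reference.** With GE known exactly, comparing the pool with sum(GE_i p_i) / sum(GE_i) gives r = 1 and a gap of 0 by construction. With an assumed log-SD of 0.7 for measurement error in GE, an error-free pool correlates 0.84 to 0.93 with the GE-weighted reference over the same range of DNA spread.

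**The case against.** The strongest reply is that the plain mean is the right target for the question asked. Objective seven is whether pooling can replace individual examination to save cost, and the protocol's own SNP association analyses use individual frequencies with no weighting stated. If a pool does not reproduce their average, that is real disagreement for the substitution decision. This stands. A reader might infer that the planned reference is an error to be replaced, but the protocol does not support that. The gap is a missing second comparison.

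A reader might also infer that the weighting would pass unnoticed, or that pooling would be wrongly rejected. Neither follows. The planned statistics respond to the weighting, through a correlation below 1 or a mean difference. The article sets no correlation threshold for rejecting pooling and does not say that a discrepancy will be blamed on the assay. What is lacking is attribution.

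The low correlations need one expected SNP frequency in every pool. The sites were chosen for differing drug pressure, and the Discussion expects SNP frequency to rise with it if the SNPs play a role, which would raise r. The Discussion also concedes that resistance may not yet have emerged, in which case both quantities may be near zero. A link between SNP frequency and DNA quantity is an assumption here; the protocol reports none.

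Finally, S10 Info is not shown and may fix the composition of pools or some equalisation of DNA, and the absence of weights is read from the word mean. These limits reduce confidence in the size. They do not make the planned comparison able to separate the two sources of disagreement.

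**Conclusion.** The point holds in a limited form. As the article describes pooling, an error-free pool estimates a DNA-weighted mean. The only planned reference is the mean of individual frequencies, so Pearson's r and per-pool differences mix assay or pooling failure with weighting by infection intensity.

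The effect on r ranges from negligible (about 0.99) to large (about 0.50), depending on the spread of DNA quantity and on how far expected SNP frequency differs between pools. None of these inputs is in the protocol, so no single value should be quoted as the expected result. The permutation test on mean frequencies is systematically affected only if SNP frequency is related to DNA quantity.

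The consequence is confined to the pyrosequencing part of the pooling objective. The equivalence of egg reduction rates, diagnostic performance, the SNP association analyses on individual samples and the qPCR pooling comparison are untouched.

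**What to change.** Keep the planned comparison with the unweighted mean, and describe it as the test of whether a pool can replace the average of individual results.

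Add a comparison of each pool with the GE-weighted mean of its individual SNP frequencies, sum(GE_i p_i) / sum(GE_i), using the GE that qPCR already measures on the individual extracts. Report the weighted-minus-unweighted gap per pool and overall, as the part of any disagreement due to intensity weighting. For hookworm, state which species' GE is the weight, because qPCR measures *N. americanus* and *A. duodenale* separately while pyrosequencing samples are selected for hookworm as a group.

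The cost is one weighted mean per pool and some extra reporting, with no added laboratory work. Measurement error in GE will keep the weighted agreement below 1 even for a perfect assay. The weighted result should be read with that in mind and not as a pass mark of 1.
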